#### Esports performance.

To comprehensively evaluate the objective operational skills, we utilized a specialized FPS training software called Aim Lab. Aim Lab is a free PC application designed to enhance aiming performance in FPS games. It offers comprehensive testing, training, and analysis features tailored to assess and improve players’ aiming abilities. Aim Lab has been employed in research on esports performance within the FPS gaming domain [68,69]. We selected five types of skill tests that are highly relevant to shooting games: flicking, tracking, accuracy, detection, and speed. Specifically, flicking capacity and detection capacity will be quantified by the total number of targets successfully hit during their respective 1-minute tasks. Tracking performance will be measured by the total time (in seconds) the participant successfully keeps the crosshair locked onto a moving target during the 1-minute tracking task. Furthermore, overall shooting accuracy and reaction speed will be evaluated. Accuracy will be calculated as the average hit rate (the percentage of successful hits out of total shots fired), while speed will be determined by the average reaction time (in milliseconds), with both metrics derived from the combined data of the flicking and detection tasks.

Choosing to use a third-party shooting program for testing instead of a specific game's custom approach has several advantages. Firstly, it ensures that all shooting game players have the same level of familiarity with the testing program, preventing individual players from obtaining higher esports performance scores due to their proficiency in a chosen game. Secondly, Aim Lab is primarily a training program focused on practice rather than entertainment, and it is unlikely that casual players would engage in regular training with this program. By selecting this software, we can avoid the potential influence of players’ habitual use of Aim Lab during the 12-week intervention, which could enhance their proficiency and subsequently affect the final performance test. Additionally, we excluded habitual users of Aim Lab during the screening phase to mitigate this issue. On the other hand, using a specific mainstream shooting game for testing would make it difficult to control the spontaneous participation of players who are loyal users of those games during the 12-week intervention, leading to an increase in proficiency and potentially affecting the final game performance test. Furthermore, Aim Lab, being a dedicated shooting training and testing software, provides detailed test scores for different dimensions of shooting, such as reaction time and accuracy. Compared to previous studies that used custom modes within specific esports games for testing, using Aim Lab offers a more objective approach, avoiding subjective factors or errors dependent on assessors [27].

Before the Aim Lab test begins, each participant will undergo a warm-up session to familiarize themselves with the software, mouse, and keyboard setups. Razer Synapse will be used to help participants set the DPI (Dots per inch). All Aim Lab tests will be conducted on the same computer in our laboratory, using identical mouse and keyboard setups.

Considering the enhancement of psychological qualities in participants through physical exercise, as well as the correlation between esports performance and psychological skills, we have implemented three types of psychological tests in addition to the operational gaming tests. These tests include psychological skill use, self-regulation, and mental toughness. These psychological measures, specifically psychological skill use, self-regulation, and mental toughness, have been demonstrated in previous research to have significant correlations with gaming performance and competitive abilities in esports players [59,60]. The Self-Regulation Questionnaire (SRQ) [70,71], Test of Performance Strategies-2 (TOPS-2) [72], and Sports Mental Toughness (SMTQ) [73] will be used, and these qualities were proven to be correlated with esports performance [59,74]. To ensure accurate comprehension by the participants, bilingual (English-Chinese) versions of these instruments were administered. The Chinese translations of these scales have been previously validated and have demonstrated robust psychometric properties, including excellent internal consistency and structural validity, within Chinese populations [75–77]. SRQ is composed of 63 items divided into six distinct dimensions: evaluating, triggering, searching, planning, implementing, and assessing. Responses to the SRQ are measured using a 5-point Likert scale. TOPS-2 features a total of 64 questions, split evenly, with 32 focused on competitive scenarios and another 32 pertinent to practice settings. For the purposes of our research, we exclusively considered the subset of questions that pertain to competitive contexts. The TOPS-2 encompasses a range of nine psychological dimensions that are believed to influence performance. These include the establishment of objectives, the use of mental imagery, techniques for achieving calmness, methods of energy management, internal dialogue practices, management of emotions, the development of automated responses, patterns of pessimistic thought, and susceptibility to distraction. However, in this investigation, the susceptibility to distraction was omitted from the analysis based on prior studies that have indicated its lower reliability in terms of internal consistency [72]. The SMTQ is a 14-item instrument that was established to ascertain athletes’ mental toughness levels. SMTQ is structured into three distinct subsections: it includes a set of six questions aimed at assessing confidence, another four that measure steadiness, and an additional four items dedicated to evaluating an individual’s level of self-regulation.

#### Body composition and anthropometry.

Body composition will be assessed using a multi-frequency bioelectrical impedance analyzer (MC-780MA, Tanita Corporation, Tokyo, Japan). Key parameters extracted will include body weight, body mass index (BMI), fat mass and percentage, as well as total and regional (upper and lower limb) muscle mass.

Additionally, specific anthropometric data will be recorded. Waist and hip circumferences will be measured using a standard non-elastic tape. Furthermore, considering the specific operational demands of esports, participants’ hand dimensions, including finger length, palm length, and palm width, will be precisely measured. These hand anthropometrics are collected to account for physical traits that may potentially influence mouse-grip mechanics and gaming operational performance.

#### Physical competence.

In this domain, six variables will be measured using well-established and standardized field tests. These include maximal oxygen consumption (VO2max), grip strength, core strength, body balance, agility, and flexibility. VO2max will be assessed through PACER (Progressive Aerobic Cardiovascular Endurance Run) 20-m [78,79]. Grip strength will be measured with a handgrip dynamometer [80]. The core strength, static balance, agility, and flexibility will be measured, respectively, through the Plank Test [81], Unipedal Stance Test [82], Agility T-Test [83], and Shoulder Reach Test [84].

To prevent mutual impact, the test of physical competence will be conducted on a different day from the assessments of esports performance. There will be a minimum 48-hour gap between these two sets of assessments.

#### Perception.

Beyond the aforementioned quantitative metrics, we will conduct supplementary, semi-structured interviews following the completion of the 12-week intervention. We will invite all participants from the two exercise intervention groups (HIIT and MICT) who consent to engage in subsequent dialogues. Because this assessment is strictly tied to the intervention, the sample size is predetermined by the number of intervention completers. Consequently, participant recruitment is not dictated by traditional qualitative data saturation criteria. The interviews will be highly open-ended, with the primary guiding question being: “How do you perceive the 12-week exercise intervention has affected your in-game esports performance?”. Follow-up probing questions will be used to encourage participants to elaborate on specific subjective feelings, such as perceived changes in focus, fatigue, or operational mechanics. The impetus for this supplementary qualitative method is twofold: firstly, to explore participants’ subjective expectations to evaluate potential expectancy effects stemming from the lack of participant blinding; and secondly, to capture subjective experiences that can offer valuable directional insights and hypotheses for future research in this under-investigated field.

#### Affect.

Before the esports performance assessment, participants are required to fill out the bilingual (English-Chinese) version of the International Positive and Negative Affect Schedule Short Form (I-PANAS-SF) [85]. This scale was used to determine whether short-term exercise-induced changes in affect influenced video game performance. The I-PANAS-SF is a brief, self-reported questionnaire that consists of two 5-item scales (10 items in total) to measure both positive and negative affect. The Chinese version of the I-PANAS-SF has also been validated, demonstrating excellent internal consistency and cross-cultural measurement invariance within Chinese populations [86].

#### Physical activity and sitting time.

The evaluation of both physical activity and sitting time will be conducted through the bilingual (English-Chinese) version of the self-administered International Physical Activity Questionnaire (IPAQ) long form. This is a widely used instrument, and its Chinese translation has well-established reliability and validity among Chinese cohorts [87,88]. This specific version of the IPAQ comprises a set of 27 questions designed to ascertain the duration (in minutes) of participants’ involvement in physical activities of different intensity levels.

Moreover, to prevent the inclusion of participants who already had a regular habit of engaging in aerobic exercise, spontaneously engaging in additional aerobic exercise during the 12-week intervention period that could potentially influence the final test results, we excluded players who already had a regular habit of engaging in cardiovascular exercise during the recruitment process.

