### Measurements

To comprehensively evaluate the effects of the 12-week exercise intervention, the measurements in this study are systematically categorized into primary outcomes, secondary outcomes, exploratory outcomes, and control and monitoring variables. The core construct of our investigation is esports performance, which we conceptualize as a multidimensional framework comprising both objective operational skills and esports-related psychological skills. To implement our multidimensional evaluation of esports performance while maintaining strict statistical rigor, the primary outcome is specifically defined as flicking capacity in esports performance (quantified by the total number of targets successfully hit during a 1-minute task). This metric was strategically selected as the primary endpoint because it effectively captures “aiming throughput”, inherently accounting for the speed-accuracy trade-off by rewarding both speed and precision.

The secondary outcomes encompass the remaining dimensions of our esports performance framework, including other operational metrics (detection capacity, tracking performance, overall shooting accuracy, and reaction speed) and esports-related psychological skills, as well as body composition and physical competence.

Other outcomes were strategically selected to support and enhance the validity of our primary analysis while maintaining a clear focus on the main research objectives. These measures serve three specific purposes: (1) to identify and control for potential confounding variables through covariate analyses, ensuring robust assessment of the exercise’s effect on esports performance; (2) to monitor and standardize key lifestyle factors (e.g., sleep, affect, physical activity, and dietary intake) known to influence cognitive and gaming performance, thereby isolating the intervention effect; and (3) to enable supplementary analyses exploring potential mechanisms underlying the relationship between physical exercise and esports performance.

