### Intervention

From previous literature, it has been observed that a HIIT protocol involving 10 × 1-minute bouts at 80–90% of maximum heart rate (HRmax) with 1-minute recovery periods at 40–50% of HRmax is deemed effective [92–94]. Moreover, this intensity and interval have shown significant short-term effects on esports performance in previous studies [27]. This study will follow this protocol for the HIIT exercise group. MICT in this study will consist of continuous exercise at 64–76% of HRmax for 20 minutes, ensuring that the total exercise duration is equivalent to the HIIT protocol to maintain comparable training volumes between groups. A standardized 3-minute warm-up with dynamic stretching and a 3-minute cool-down at 50% HRmax will be added at the beginning and end of each exercise session for both intervention groups. Participants in both intervention groups will be required to complete their respective exercise protocols three times per week throughout the 12-week intervention period. Real-time heart rate monitors (Polar Pacer) will be used to ensure intensity during exercise sessions. In addition, a rating of perceived exertion (RPE) will be employed in each training session utilizing the 6–20 Borg scale [95]. During high-intensity intervals, participants will be instructed to maintain an RPE between 15–18, while during the low-intensity intervals, warm-up, and cool-down phases, an RPE of 11–13 will be targeted [96]. For the MICT group, participants will maintain a moderate-intensity effort corresponding to an RPE of 12–14 throughout the continuous exercise session. Meanwhile, all training sessions will be guided by a professional fitness trainer who will ensure the professionalism and safety of the entire exercise process.

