Participants will be allowed to undertake physical exercise either on a treadmill or outdoors, encompassing exercises such as running, jogging, and brisk walking, provided they reach the stipulated heart rate. To account for the potential confounding effect of the exercise environment (indoor vs. outdoor) [97], we will utilize the built-in GPS tracking feature of the Polar Flow system to record the specific setting of each session. This environmental factor will be considered as a covariate in our subsequent statistical analysis. During the initial three sessions, participants will be obliged to exercise in a laboratory under the guidance and supervision of research staff. This ensures not only a precise understanding and execution of the training regimen but also the safety of participants during subsequent unsupervised exercises. Once it is ascertained that participants can meet the training benchmarks without supervision, they are permitted to carry out their exercises at home in a free-living setting for the remainder of the intervention. During these home-based exercises, participants are required to wear a heart rate monitor to track exercise intensity. The monitor records the exercise data throughout the training program, and with prior consent obtained from participants, we will monitor each participant’s exercise data through the *Polar Flow for Coach*, including metrics such as heart rate, frequency, and running speed to confirm participants’ compliance with the exercise plan. Specifically, we define “adherence” using a dual-criterion approach based on both heart rate compliance and session completion. A single training session will be considered “valid” if the participant meets the specific heart rate prescription: for the HIIT group, achieving the target high-intensity zone for at least 80% of the intervals; for the MICT group, maintaining the target heart rate zone for at least 80% of the continuous exercise duration. Consequently, overall adherence to the exercise protocol is defined as the successful completion of at least 80% of the total prescribed valid sessions. This flexible, home-based research design, combined with remote monitoring, aims to further mitigate participant drop-out rates in longer-term interventions and construct an exercise intervention model that can be implemented long-term in a living environment rather than in a laboratory setting, and the methodological approach has also been employed in prior studies [92,98].

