### Data analysis

An intention-to-treat (ITT) analysis will be conducted as our primary analytical approach to evaluate the overall effectiveness of the intervention. Additionally, a per-protocol analysis will be performed as a sensitivity analysis, which will only include participants who met the predefined adherence criteria. Missing data will be addressed using the Multiple Imputation by Chained Equations (MICE) technique. The normality of the data will be assessed using the Shapiro-Wilk test, and Levene’s Test will be used to assess the homogeneity of variances. Continuous variables will be presented as means with standard deviations (SD) or medians with interquartile ranges (IQR), depending on their data distribution. Categorical variables will be presented as frequencies and percentages. Baseline characteristics among the three groups will be compared using a One-way Analysis of Variance (ANOVA) for normally distributed continuous variables, a Kruskal-Wallis H test for non-normally distributed continuous variables, and Chi-square tests for categorical variables.

To test the main hypothesis, the primary outcome is defined as flicking capacity. Generalized Estimating Equations (GEEs) will be used to determine the group-by-time interaction effect for both the primary and secondary longitudinal outcomes. To rigorously specify the GEE models, the distributional family and link function will be selected based on the specific nature of each outcome variable. An exchangeable working correlation structure will be specified to account for the within-subject correlation of repeated measures across time points. Furthermore, robust standard errors (the sandwich estimator) will be utilized to ensure valid statistical inference even if the working correlation structure is misspecified.

Furthermore, changes in monitored lifestyle variables (i.e., dietary intake, physical activity, and sleep quality) over the intervention period will be evaluated. If any of these variables exhibit significant changes or between-group imbalances, they will be incorporated as covariates in the GEE models to adjust for potential confounding effects, thereby isolating the true effect of the exercise interventions.

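### The plan does not separate prescribed HIIT and MICT sessions from IPAQ answers, so compliance alone can trigger covariate adjustment, and exercisers cutting other activity can go unseen

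*Protocol article*

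**What the plan says.** Under Physical activity and sitting time, the protocol article names one activity questionnaire, the "self-administered International Physical Activity Questionnaire (IPAQ) long form", "designed to ascertain the duration (in minutes) of participants’ involvement in physical activities of different intensity levels". Experimental design says that all groups report physical activity and that controls receive no intervention. Measurements gives the purpose of such variables, which includes "to monitor and standardize key lifestyle factors (e.g., sleep, affect, physical activity, and dietary intake", so that the effect of the intervention can be isolated.

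Intervention prescribes sessions "three times per week throughout the 12-week intervention period". Each has 20 minutes of HIIT or MICT plus a 3-minute warm-up and a 3-minute cool-down. On the heart-rate device it says: "The monitor records the exercise data throughout the training program". That record is used to confirm compliance.

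Data analysis then states that "changes in monitored lifestyle variables (i.e., dietary intake, physical activity, and sleep quality) over the intervention period will be evaluated". A variable that shows a significant change or a between-group imbalance becomes a covariate in the GEE models.

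The article does not say whether study sessions are to be included in the IPAQ answers or left out. It does not link the device record to the questionnaire, and it does not say which IPAQ summary is used.

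**The concern.** The variable is monitored in order to isolate the effect of the programme. For that purpose it should describe activity apart from the programme. A participant who trains three times a week for the study and is asked for minutes of activity by intensity would naturally report those minutes. After baseline, the questionnaire would then measure treatment plus outside activity in two arms and outside activity alone in the third.

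This matters because a stated decision rule acts on the variable. The rule may respond when nothing has happened except that participants complied, and the model is then adjusted for a post-randomization variable that contains the treatment. Such adjustment can absorb part of the effect being estimated. The rule may also stay silent when activity outside the programme has shifted between arms.

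A later analysis plan can only partly repair this. What participants are told to include is settled when the data are collected, and an omitted instruction cannot be recovered from the questionnaire alone.

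**Working it through.** The plan gives no figure of its own for this point, so there is nothing to reproduce. The check is arithmetic on the prescribed sessions, followed by scenarios.

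**Prescribed minutes (Intervention section)**
- Core exercise: 3 sessions x 20 min = 60 min/week. For HIIT, 10 x 1 min plus 10 x 1 min recovery is also 20 min.
- With warm-up and cool-down: 3 x (3 + 20 + 3) = 78 min/week.
- At the adherence threshold: 36 sessions x 0.80 = 28.8, so 29 sessions. Then 78 x 29/36 = 62.8 min/week, or 60 x 29/36 = 48.3 min/week for the core part.

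**Scenarios**

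Assume full adherence and full reporting of sessions. Then:
- reported change in an exercise arm = 78 + change in outside activity
- reported change in controls = change in outside activity

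All values are expected changes in min/week.

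| Scenario | Reported change, exercise arm | Reported change, control | Reported difference | True difference in outside activity |
|---|---|---|---|---|
| (a) No outside change | +78 | 0 | +78 | 0 |
| (b) Controls take up 78 | +78 | +78 | 0 | -78 |
| (c) Exercisers cut 78 elsewhere | 0 | 0 | 0 | -78 |
| (d) Exercisers add 78 | +156 | 0 | +156 | +78 |

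Reading the table against the Data analysis rule:
- (a) Both conditions, change and imbalance, can be met although outside activity is unchanged.
- (b) The imbalance condition is silent. The change condition can still respond, because the control arm rises by 78.
- (c) Neither condition responds.
- (d) The imbalance shows, but how much of the 156 is extra activity can be told only from the device record.

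**How readily compliance alone is flagged as imbalance**

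The SD of the IPAQ quantity compared is not in the document and is assumed here. For one exercise arm against control with n = 52 per arm, two-sided 5%:

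power = Phi(78 / (SD x sqrt(2/52)) - 1.96)

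For SD = 200: 78 / (200 x 0.196) = 1.99, and Phi(0.03) = 0.51.

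| Assumed SD (min/week) | Chance of a flag, 78 min/week | Chance of a flag, 60 min/week |
|---|---|---|
| 120 | 91% | 72% |
| 200 | 51% | 33% |
| 300 | 26% | 17% |
| 400 | 17% | 12% |

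Whether the primary model is adjusted would thus depend largely on the spread of a self-reported measure. These figures cover the imbalance condition only. The within-arm change condition is a second route to the same adjustment.

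**The case against.** The strongest reply is that this is silence, not error. Questionnaire instructions and scoring are details that an article commonly leaves to the full protocol. That stands as far as it goes: the article does not say that sessions are counted, and it mentions no IPAQ total. A reader might infer that the plan uses a total that includes the prescribed sessions. The text does not establish this, so the point is conditional on sessions being reported. It goes beyond missing detail because the article does fix a rule that acts on the variable.

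A reader might also infer that the IPAQ cannot show extra exercise at all. That is too strong. Controls have no study sessions, so their answers contain only outside activity and a rise from baseline could be seen. In the exercise arms the Polar Flow records would allow outside activity to be recovered if dates are matched. The article simply does not say this will be done.

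The phrase "spontaneously engaging in additional aerobic exercise during the 12-week intervention period that could potentially influence the final test results" might suggest that the IPAQ is assigned to detect such exercise. It belongs to a sentence about eligibility, which ends by saying that "we excluded players who already had a regular habit of engaging in cardiovascular exercise during the recruitment process". The role given to the measure is the general monitoring one in the Measurements section. Exclusion at recruitment cannot show what changes after randomization, though.

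Finally, under intention-to-treat, activity displaced after assignment is part of the effect of assignment and does not bias the randomized comparison. That also stands. Recruits without a regular exercise habit may have little structured exercise to drop, although the questionnaire covers physical activity more broadly. The harm therefore lies in the covariate rule and in the interpretation of the monitoring variable. The unadjusted comparison is not affected.

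**Conclusion.** The point holds in a limited form. As written, a decision rule acts on a measure that can contain 60 to 78 min/week of the treatment itself in the two exercise arms (about 48 to 63 at the adherence threshold). If sessions are reported, compliance alone can bring that measure into the GEE as a covariate. Under the assumed SDs of 120 to 400 min/week, the chance of this through the 78 min/week imbalance alone runs from 91% down to 17%. Exercisers who reduce other activity by about the prescribed amount would meet neither condition. Uptake by controls would be hidden between arms but could be visible within the control arm.

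The conclusion assumes that participants include the sessions in their answers and that no instruction in an unseen document says otherwise. The document gives no basis for how often compensation or control uptake occurs, or for how far adjustment would move the estimate for flicking capacity. It does not support a claim that the primary randomized comparison is itself biased. This should be corrected, but it does not touch the definition of the primary endpoint.

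**What to change.** - At each post-baseline IPAQ, instruct HIIT and MICT participants to leave out the study sessions. Alternatively, subtract the Polar Flow session minutes that fall within the recall period.
- Define the physical-activity variable in the Data analysis section as non-study activity, and compare that across the three arms.
- Report prescribed-session minutes separately as dose received.
- State that IPAQ values that include study sessions will not enter the primary GEE as a covariate.

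The cost is one line on the questionnaire, or a subtraction using data already collected, plus a sentence or two in the analysis section. There are two downsides. Participants may not separate study from other activity perfectly, and the subtraction works only if recall dates are matched to the device records. Non-study activity is still measured after randomization, so whether it belongs in the primary model remains a separate question that this change does not settle.
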